**Table 2 Tab2:** **Study schedule and assessments**

	t = wk 0	t = wk 1-2	t = wk 2-3	t = wk 26-27	t = wk 27-28
Activity/Assessment	Pre-study screening (phone)	Study visit 1 (Screening/Baseline)	@ home	Study visit 2 (post-intervention)	@ home
**Inclusion/Exclusion criteria**					
Cardiovascular risk factors					
Rose questionnaire	x				
Physical exam & ECG		x		x	
MMSE		x			
LAPAQ outdoor	x				
H&Y stage		x		x	
**Primary outcome**					
**Motor symptoms**					
MDS-UPDRS III *off*		x		x	
**Secondary outcomes**					
**Motor symptoms**					
MDS-UPDRS III *on*		x		x	
MDS-UPDRS IV		x		x	
TUG		x		x	
Pegboard		x		x	
Finger tap test		x		x	
Mini-BESTest		x		x	
Falls & Near-falls		x		x	
**Non-motor symptoms**					
TAP flexibility		x		x	
TMT		x		x	
MoCa		x		x	
SCOPA-sleep			x		x
HADS			x		x
SCOPA-AUT			x		x
FSS			x		x
**Quality of life**					
PDQ-39			x		x
**Physical fitness**					
VO2max		x		x	
6MWT		x		x	
**Adherence**					
Bike computer/motivational app data		Data is automatically collected after each workout on a secured server. After 6 months the data is archived and locked.			

ECG = electrocardiogram. MMSE = Mini Mental State Examination, LAPAQ = Longitudinal aging study Amsterdam Physical Activity Questionnaire. H&Y = Hoehn & Yahr, MDS-UPDRS III/IV = Movement Disorders Society-sponsored revision of the Unified Parkinson’s Disease Rating Scale, motor section (III) and motor complications section (IV). TUG = Timed Up and Go test. Mini-BESTets = Mini-Balance Evaluation System Test. TAP = Test of Attentional Performance. TMT = Trial Making Test. MoCa = Montreal Cognitive Assessment. SCOPA-sleep = SCales for Outcomes in PArkinson’s disease, sleep section. SCOPA-aut = SCales for Outcomes in PArkinson’s disease, autonomic function section. FSS = Fatigue Severity Scale. PDQ-39 = 39-item Parkinson Disease Questionnaire VO2max = maximal amount of oxygen inhaled during maximal graded test. 6MWT = 6 Minute Walk Test.

#### General variables

The following data are collected at baseline: age at baseline, gender, education, age at onset and disease duration. Details on Parkinson medication (i.e., drug name, dose, frequency, levodopa equivalence) will be collected during both visits using a customized form.

#### Primary outcome measure

The primary outcome will be the score on the motor section of the Movement Disorders Society-sponsored revision of the Unified Parkinson’s Disease Rating Scale (MDS-UPDRS) [18] after 6 months measured in the *off* state. The UDPRS is the most widely used, well-validated, clinical rating scale for PD and has been shown to be sensitive to change in clinical status [21] and data on clinical important differences are available [22,23]. Based on these data we considered a change of minimal 3.5 clinically important. Clinical progression appears to be faster and UPDRS motor score increases steeper in early stages of PD [24-26], underlining the need for treatments that can reduce the UPDRS motor score in these stages and slow down the disability rate. As intra-rater variability is lower compared to inter-rater variability [27] the same rater will perform the MDS-UDPRS-III assessments at baseline and follow up.

#### Secondary outcome measures

##### Additional motor symptoms

To test the impact of the intervention on motor symptoms during everyday life, the MDS-UPDRS III is also assessed in the *on* state. Balance deficits will be analyzed with the short version of the Balance Evaluation System Test (Mini-BESTest). The Mini-BEST test is a clinical tool that is highly correlated with the validated and generally accepted Berg Balance Scale, but is more suitable for mild PD as it has no ceiling effect [28]. Balance impairment is defined as a score of ≥21 on the Mini-BESTest [29]. The Timed Up and Go test (TUG) will be used to test mobility. The TUG measures the ability of patients to perform sequential locomotor tasks that incorporate walking and turning. It has been validated in PD and is sensitive to changes in mobility in PD patients [30]. The Dexterity device of the Objective Parkinson’s Disease Measurement system will be used to quantify bradykinesia with a digitography (keyboard) test, and complex motor functioning is tested with a pegboard test.

Motor complications and (near) falls will be assessed by questionnaires. Falls and near-falls will be registered retrospectively over a period of 6 months with an interview-based questionnaire that is used in clinical practice by physiotherapist specialized in PD [31]. Even patients with early disease may already experience fluctuations in their response to levodopa [32]. Therefore, motor complications will be evaluated as well, using the interview-based MDS-UPDRS IV questionnaire.

##### Non-motor symptoms

Several studies report beneficial effects of aerobic exercise on cognitive function in healthy elderly [33]. During the in-person assessments several cognitive tests will be performed. The Montreal Cognitive Assessment scale (MoCa) is used for a quick screening of global cognitive function. It has been widely accepted for use in PD populations [34] by assessing multiple domains of cognitive function including memory, language, complex visuospatial processing, and executive function. The MoCa is suggested to be more sensitive to cognitive impairment in PD and to temporal changes compared with the MMSE [35]. One of the earliest cognitive deficits in PD is executive function (set-shifting in particular) [36]. We will perform two tests to assess set-shifting in *off* state: the flexibility subset of the Test of Attentional Performance (TAP 3.2) and the Trail Making Test (TMT) A and B. In the flexibility subset of the TAP test two verbal stimuli (letter-number) are simultaneously presented on a computer screen and the patient has to press the button on the side of the target stimulus. The target stimulus will either be fixed (requiring a response to the side of letters or numbers only) or alternating (requiring a response that alternates between letters and numbers). A similar non-computerized version of this task has been used before in PD and shown to be highly specific for task-set shifting in PD patients in *off* state [37]. The TMT is one of the most frequently used paper and pencil test in clinical practice and consists of two parts: one assessing psychomotor speed (A) and one assessing mental flexibility (B) [38]. Also in PD the TMT is able to indicate deficits in set shifting [39]. For all three cognitive tests parallel versions will be used at follow up, to minimize learning effects.

Several studies in non-PD populations indicated beneficial effects of aerobic exercise on mood [40,41], sleep [42], constipation [43] and fatigue [44]; all of which are part of the non-motor symptoms that PD patients may experience. We will use self-rating questionnaires that are completed at home to assess these non-motor symptoms. Mood will be assessed with the Hamilton Anxiety and Depression Scale (HADS). This is a 14-item scale assessing both depression and anxiety and has been validated in PD patients [45]. The section on sleep of the Scales for Outcomes in Parkinson’s disease (SCOPA-Sleep) will be used to measure sleep disturbances. This a short practical self-rating scale designed to evaluate sleep quality and daytime sleepiness [46]. Autonomic symptoms can be assessed with the SCOPA-autonomic (SCOPA-AUT) [47]. For the purpose of this trial only the gastro-intestinal section of the SCOPA-AUT will be used to assess constipation. Fatigue will be addressed by the Fatigue Severity Scale (FSS), which has been recommended for screening and severity rating in PD by the movement disorders society [48].

##### Quality of life

Quality of life will be assessed with the 39-item Parkinson Disease Questionnaire (PDQ-39), a PD specific self-administered questionnaire [49]. Participants are asked to fill out this questionnaire at home.

##### Physical fitness

Physical fitness is measured using the 6-minute walk test and the maximal aerobic power tested by indirect calorimetry (VO2max) during the maximal graded exercise test. The 6-minute walk test is widely used to assess functional exercise capacity and normative values for PD patients exist [50]. The VO2max is the gold standard of cardiovascular fitness and is a reliable and repeatable measure in subjects with mild to moderate PD [51].

##### Adherence

Adherence will be determined based on the number of dropouts and the training frequency in both groups, as well as the total time exercised within the prescribed heart rate zone in the intervention group.

### Interventions

The total duration of the intervention will be 6 months, regardless of group allocation. All patients will be supported by the same coach during their intervention.

#### Aerobic exercise (intervention group)

The intervention is multifaceted and consists of a unique combination of home-based aerobic exercise, enhanced with virtual reality software and real-life videos, the use of a motivational app and coaching with tele-monitoring from a distance. Aerobic exercise, performed on a stationary home trainer, forms the basis of the intervention. The home trainer is connected to an all-in-one computer equipped with software (Simultrainer Europe Ltd.) that provides visual feedback and virtual coaching (together with the aerobic workout, this combination is referred to as “exergaming”). Patients are instructed to train at least 3 times a week for 30–45 minutes within a predetermined heart rate zone. The heart rate zone is based on the heart rate reserve (HRR), calculated with the Karvonen method; the lower bound will gradually increase from 50% to 70% of the HRR (the upper bound is set at 80%). During the training session, the actual heart rate and time exercised within the heart rate zone, is visualized providing direct feedback. The software offers the opportunity to (a) cycle classical bike routes accompanied by real-life videos of the route, (b) cycle in a virtual world in which they can compete against their own best previous performance or virtual competitors; and (c) to perform an adjusted arcade game that is driven by the patient’s cycling performance. Taken together, this serves to motivate the patients *during* the actual exercise.

In addition, we designed a customized tablet-based motivational app (Park-in-Shape app, designed by IJsfontein Interactive Media Ltd.) to motivate patients both *before* and *after* the actual exercise. Specifically, the app shows exercise goals, provides support, and gives feedback about performance. Patients can view their results in a comprehensible way and can invite supporters to track their progress. Supporters can stimulate them to reach their goals by cheering them on, complimenting them on their performance, and promising incentives when they reach one of their goals.

Every fortnight a coach will have telephone contact with the participants to check their progress, to adjust their training schedule (if necessary) and to provide support. At least every 4 weeks the training schedules are evaluated and if the patient was easily able to adhere to the prescribed heart rate zone, the heart rate zone is raised. This allows for a graded increase in the aerobic exercise and offers a reward system by setting goals. The coach can decide on the individual intervals of these fitness checks. Communication between the bike computer and the motivational app ensures that adjustments in exercise goals are immediately and correctly enforced. Data from the training sessions are automatically saved after each session and uploaded to a secured server, allowing the coach to track the progress from a distance.

#### Stretching (active control)

The control condition is designed as an ‘active control’ to increase compliance, and consists of stretching, flexibility and relaxation exercises. The exercises do not have an aerobic component and are based on previous studies in which stretching served as a control [52,53]. The core activities encompass stretches involving the upper body and lower extremities, with the use of gentle joint extension and flexion and trunk rotation. In addition abdominal breathing with an emphasis on inhaling and exhaling to maximum capacity and relaxation of major muscles will be used. Patients are instructed to do the exercises 3 times a week for approximately 30 minutes without adding other elements to the training (no dumbbells, etcetera). After randomization, the app and the first exercise program will be explained by the coach during a home visit. The rest of the time the exercises will be executed unsupervised within the patients’ home. These exercises are commonly given to patients by the patients’ physiotherapists without specific supervision, and the majority of the exercises will be performed in seated or supine position reducing the fall risk.

In order to increase comparability between the two groups, the active control group will also be supported and motivated by the coach using the same protocol as in the intervention group. This includes an adjusted version of the motivational app for the active control group. Exercises are explained in the app through text and videos, and every month a different set of exercises will be presented. Patients will note the frequency of the performed exercises in the app, allowing the coach to follow the performance of the patients on a distance. Moreover the coach can tailor the program to the individual needs.

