### Statistical analysis plan

The primary and secondary outcomes will all be analyzed with an analysis of covariance (ANCOVA). The dependent variable will be the follow up scores; group allocation, gender and treatment status will serve as fixed factors and the baseline values, age at baseline, Hoehn & Yahr stage, disease duration will serve as covariates. The analyses will be performed on an intention-treat basis. In case of any missing data, sensitivity analysis (last observation carried forward) will be used with delta-adjusting imputation [57]. It should be noted that both an improvement of symptoms in the intervention group and a worsening of symptoms in the control group are considered equally important given the neurodegenerative nature of the disease. In order to determine the optimal effect of aerobic exercise, an additional per protocol analysis will be performed including all patients who completed the program as prescribed.

Adherence to the program will be analyzed according to intention-to-treat, but adherence to the prescribed heart rate will be analyzed per-protocol as this is part of a mediation analysis. Moreover dose-effect relationship will be explored by calculating the correlation between the total exercise volume and the delta score on the different outcomes. An interim analysis will not be performed.

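### Training frequency is logged by device in the aerobic arm and self-noted in the control arm, so a between-arm test of it is confounded with how sessions are recorded

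*Protocol article*

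**What the plan says.** All references are to the protocol article.

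- **Secondary outcome measures, Adherence:** "Adherence will be determined based on the number of dropouts and the training frequency in both groups". Time within the heart rate zone is added for the intervention group only.
- **Aerobic exercise (intervention group):** "Data from the training sessions are automatically saved after each session and uploaded to a secured server". No entry by the patient is described.
- **Stretching (active control):** after one home visit by the coach, "The rest of the time the exercises will be executed unsupervised within the patients’ home", and "Patients will note the frequency of the performed exercises in the app". The coach follows these entries from a distance and supports controls by the same protocol as the aerobic arm, which includes fortnightly telephone contact.
- **Table 2, Adherence row (bike computer and motivational app):** "Data is automatically collected after each workout on a secured server". The row does not separate the arms.
- **Statistical analysis plan:** "The primary and secondary outcomes will all be analyzed with an analysis of covariance (ANCOVA"), with group allocation among the fixed factors. Further: "Adherence to the program will be analyzed according to intention-to-treat". Separately, "an additional per protocol analysis will be performed including all patients who completed the program as prescribed".

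**The concern.** One component of a secondary outcome is measured by instrument in one arm and by the patient's own note in the other. The recording method coincides exactly with allocation, so no covariate adjustment can separate the two. If controls note sessions they did not complete, their frequency is inflated. If they forget to note sessions, it is deflated. Either would look like an adherence effect of the intervention.

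Adherence is not a marginal topic here. The Background presents gaming to improve compliance as the trial's new element, and the Discussion expects the active control to raise compliance and limit dropout in its arm. A significant or null frequency comparison would be read as evidence on those claims.

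The additional per-protocol analysis is touched indirectly. Whether a control patient completed the program can, on what is described, be known only from what that patient enters or reports.

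**Working it through.** **1. Sources side by side**

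| Adherence component | Aerobic arm | Control arm | Comparable? |
|---|---|---|---|
| Dropout | Trial follow-up | Trial follow-up | Yes |
| Training frequency | Automatic session log | Patient's note in the app | No |
| Time in heart rate zone | Bike system | Not used | Not compared between arms |

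The problem is confined to the middle row. The fortnightly calls do not close the gap, since what a control patient tells the coach is also self-report.

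**2. The plan's own number per arm**

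The figure of 65 per group is used below, so it is checked first.
- Difference 3.5, SD 9, two-sided α 0.05, power 80%: n = 2 × [9 × (1.960 + 0.842) / 3.5]² ≈ 103.8, so 104 by the normal approximation. The t calculation gives 105 (power 0.801), as stated.
- ANCOVA correction: 105 × (1 − 0.7²) = 53.55. The plan states 53.
- Attrition of 18%: 53 / 0.82 = 64.6, so 65, as stated.

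These figures reproduce, and the present point does not alter them.

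**3. How sensitive a frequency test would be to the recording method (illustration)**

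The documents give no SD of session counts and no misreporting rate. Assumptions:
- 3 sessions × 26 weeks = 78 planned sessions.
- 75% truly done in both arms, that is 58.5, so the true difference is zero.
- 65 per arm, two-sample t test at two-sided 5%.
- Controls over-report by a fraction f, giving a spurious shift of 58.5 × f.

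SE = SD × √(2/65). For SD 15 this is 2.63 sessions. The probability of a significant result comes from the noncentral t with 128 degrees of freedom.

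| Over-reporting | Shift (sessions) | P(significant), SD 15 |
|---|---|---|
| 5% | 2.9 | 20% |
| 10% | 5.9 | 60% |
| 15% | 8.8 | 91% |

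At 10% over-reporting, varying the SD:
- SD 10: SE = 1.75, probability 91%.
- SD 25: SE = 4.39, probability 26%.

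A second set of assumptions, on the weekly scale, uses a true mean of 2.4 sessions per week in both arms (80% of 3) and 10% over-reporting, a shift of 0.24. The probability is 78%, 45% and 28% for SD 0.5, 0.75 and 1.0 (normal approximation).

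The test is symmetric, so under-recording by controls of the same absolute size gives the same probabilities with the opposite sign.

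**4. Per-protocol set (illustration of the caveat only)**

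Assume 80% of each arm truly follows the program: 52 of 65. If between 10% and 75% of the remaining 13 controls are counted as completers, the control set grows to between about 53 and 62 patients, of whom 2% to 16% did not follow the program. No effect on the motor score is derived from this, because the documents give nothing to derive it from.

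**The case against.** The strongest reply is that the bias is possible but not shown. No completion rate, SD or over-reporting rate stands in the article, and forgotten entries could offset or reverse over-reporting. That is correct, and it limits the claim to confounding of unknown sign and size. It does not rescue the comparison, because a test whose result cannot be attributed is uninformative in either direction.

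It can also be said that the ANCOVA sentence was not aimed at adherence, since training frequency has no baseline value to adjust for. But the text covers all secondary outcomes without exception, and it separately commits program adherence to an intention-to-treat analysis. As written, a comparison of the randomised groups is the natural reading.

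Three stronger readings are tempting and are not supported.

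- **That Table 2 contradicts the control section.** A reader might infer this from the word for automatic collection. The row names the app as well as the bike computer, and an entry typed by a patient can still be transferred and stored automatically. The row is imprecise about who creates the record; it is not false.
- **That the per-protocol arms are filtered by different rules, with a quantifiable shift in the effect estimate.** The text names no data source, threshold or heart-rate criterion for that set, and such detail is commonly left to a full protocol or analysis plan. Any figure for the shift would need assumed exclusion rates. A gap in exclusions could also arise simply because the aerobic prescription contains a heart-rate zone and the stretching prescription does not.
- **That self-notes in both arms would solve the problem.** This sets aside an objective log, adds a task in the aerobic arm, and does not ensure equal reporting: cyclists see their sessions recorded, while controls are unobserved.

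**Conclusion.** The point holds for the training-frequency component of adherence. The two recording methods are stated explicitly, they coincide with allocation, and the analysis section leads to a between-arm comparison. Any difference found, or its absence, is confounded with how sessions were counted.

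Direction and size cannot be derived from the documents. The range of 26% to 91% for a false significant result rests wholly on assumed 10% over-reporting, 75% true completion in both arms and an SD of 25 down to 10 sessions. It shows that a modest recording difference could matter at 65 per arm, not that it will occur.

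For the additional per-protocol analysis the conclusion is weaker and inferential: control completion appears to be knowable only from patient entries or reports, so that estimate should be read with this in mind. Dropout, heart-rate-zone time, the primary intention-to-treat analysis and the sample size are untouched.

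**What to change.** - Limit the formal between-arm adherence test to dropout, which does not depend on the session record.
- Report training frequency descriptively for each arm, state its source (device log or patient entry), and make no between-arm test.
- Keep the bike data for within-arm analyses, such as the planned exploration of exercise volume against change in outcome among aerobic patients.
- Add one sentence to the per-protocol analysis saying which data establish completion in each arm, and that in controls these rest on the patient's own record. A note under Table 2 that control-arm frequency is entered by the patient would be a helpful clarification.

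The cost is analysis-plan wording; no data collection changes. The loss is that the trial would offer no inferential comparison of session frequency between arms.

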#### Drop-outs and adverse events

Patients who drop out will be encouraged to complete the follow-up measurements. All adverse events will be noted in the electronic database; in case of serious adverse events the responsible authorities will be notified immediately.

